### Interventions

2.4

Due to the lack of high-quality, strongly recommended pharmacological treatments for PIC, and considering its self-limiting nature where spontaneous remission often occurs, a placebo control was selected. The placebo is a simulated version of the SFHS granules. Study participants will be randomized into either the treatment group or the control group. The treatment group will receive SFHS granules, while the control group will receive SFHS simulators (placebo). Both will be administered orally, three times daily, for a continuous duration of 14 days. Both the SFHS granules and their corresponding placebos are manufactured by Guangdong Efong Pharmaceutical Co., Ltd. All medications were identical in appearance and packaging, and were labeled in a blinded manner. Each code corresponds to a unique drug allocation number in the randomization list. Each medication box contains 48 sachets (42 g per sachet) of either SFHS granules or the placebo, dispensed in a single batch upon completion of screening and enrollment. During subsequent follow-up visits, the number of used empty packages and remaining medications will be recorded to monitor compliance.

SFHS granules consist of *Ephedrae Herba* (Mahuang), *Armeniacae Semen Amarum* (Kuxingren), *Cicadae Periostracum* (Chantui), *Perillae Fructus* (Zisuzi), *Peucedani Radix* (Qianhu), *Arctii Fructus* (Niubangzi), *Stemonae Radix* (Baibu), *Acori Tatarinowii Rhizoma* (Shichangpu), *Magnoliae Officinalis Cortex* (Houpo), *Citri Reticulatae Pericarpium* (Chenpi), *Atractylodis Rhizoma* (Cangzhu), *Angelicae Sinensis Radix* (Danggui), and *Glycyrrhizae Radix et Rhizoma* (Gancao). The placebo contains starch, dextrin, and 5% SFHS granule components to ensure similarity to the SFHS granules in color, odor, taste, shape, and texture.

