#### Primary outcome

2.6.1

The primary outcome measure is the cough relief rate after 14 days of treatment. Cough relief is defined as a total CSS (daytime + nighttime) ≤ 2, sustained for at least 48 h ± 2 h. Cough cure is defined as a total CSS (daytime + nighttime) ≤ 1, sustained for at least 48 h ± 2 h. The CSS will be recorded at baseline and daily throughout the study. The inter-group difference in the 14-day cough relief rate will be evaluated according to these diagnostic criteria.

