#### Investigator-initiated withdrawal

2.8.1

Investigator-initiated withdrawal refers to the removal of a randomized participant from the trial by the investigator due to circumstances that make it inappropriate for the participant to continue. Such participants will be withdrawn and provided with alternative treatments. Reasons include, but are not limited to: (1) Clinical changes: Development of severe comorbidities, complications, or specific physiological changes during the trial that, in the investigator’s judgment, render the participant unfit for continued participation. (2) Safety concerns: Occurrence of a serious adverse event (SAE) or other safety issues that necessitate the cessation of the trial intervention according to the investigator’s assessment. (3) Blinding violations: Cases involving premature unblinding or emergency unblinding must be withdrawn from the study.

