#### Participant-initiated withdrawal

2.8.2

Participants have the right to withdraw from the trial at any time. This includes: (1) Withdrawal of consent: The participant explicitly requests to terminate their participation in the trial. (2) Loss to follow-up: The participant does not explicitly withdraw but stops receiving the study medication or attending scheduled assessments and is subsequently lost to follow-up. All participants who discontinue the study early, except in cases of loss to follow-up, should complete subsequent visits according to the study schedule until the study endpoint.

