### Statistical analysis

2.10

Statistical analyses will be performed using SAS version 9.4 or a higher version.

The analysis populations are defined as follows: the Full Analysis Set (FAS) includes all randomized subjects who receive at least one administration of the investigational drug; the Per Protocol Set (PPS) includes all subjects in the FAS who comply with the study protocol, demonstrate good compliance, have complete primary efficacy endpoint data, do not use concomitant medications affecting efficacy evaluation, and have no major protocol deviations; the Safety Set (SS) includes all subjects who receive at least one administration of the study drug after randomization and have safety assessment data, and will be used as the safety analysis population.

Primary efficacy endpoint analysis: the primary endpoint is the cough relief rate on Day 14, defined as the proportion of subjects with a CSS total score ≤2 at the Day 14 visit and maintained for 48 h ± 2 h. Regardless of whether subjects experience transient relief during the treatment period, the final determination will be based on the CSS status at the Day 14 visit. This endpoint is a binary outcome and will be analyzed using the Cochran–Mantel–Haenszel (CMH) χ^2^ test stratified by center as the primary analysis model, separately in the FAS and PPS populations. Differences in relief rates between groups will be estimated using risk difference (RD), with point estimates, corresponding two-sided 95% confidence intervals, and *p* values reported. In addition, supplementary Logistic regression analyses will be performed with treatment group, center, and baseline CSS score as covariates to assess the robustness of the primary conclusions after covariate adjustment. For missing data of the primary endpoint, the Last Observation Carried Forward (LOCF) method will be used as the primary handling approach. To evaluate the robustness of the primary conclusions under assumptions regarding missing data, multiple imputation (MI) sensitivity analyses will be conducted under the Missing At Random (MAR) assumption, using baseline CSS score, treatment group, center, and all available post-baseline observations as imputation variables to impute missing values. The results obtained from both methods will be reported and compared simultaneously.

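### LOCF as the primary missing-data rule conflicts with the rule that Day 14 status decides the primary endpoint, and can bias the comparison either way when dropout is unequal

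*Protocol article*

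**What the plan says.** Section 2.10 (Statistical analysis) describes the primary relief rate in these words: "defined as the proportion of subjects with a CSS total score ≤2 at the Day 14 visit and maintained for 48 h ± 2 h". It sets aside relief that comes and goes during treatment: "the final determination will be based on the CSS status at the Day 14 visit". For missing values of this endpoint, "the Last Observation Carried Forward (LOCF) method will be used as the primary handling approach". The only other planned approach is that "multiple imputation (MI) sensitivity analyses will be conducted under the Missing At Random (MAR) assumption". The imputation model is to include baseline CSS, treatment group, center and all available post-baseline observations. Both sets of results are to be reported and compared.

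Three other places bear on the point:

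- Section 2.6.1 (Primary outcome): "The CSS will be recorded at baseline and daily throughout the study". The last available score can therefore come from any day before Day 14.
- Section 2.4 (Interventions) justifies the placebo control by "considering its self-limiting nature where spontaneous remission often occurs".
- Section 2.3.1 (Inclusion criteria) requires a CSS of at least 3 at entry, so a carried baseline score always counts as not relieved.

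**The concern.** The endpoint rule and the missing-data rule answer different questions. The first says that only Day 14 status counts. The second lets an earlier score stand in for it.

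This can go wrong in two ways. A participant whose last recorded total was 2 or less, and who then left, can be classed as relieved at Day 14 on the kind of passing relief the endpoint disregards. If the raw score is what is carried, it also appears to satisfy the 48-hour condition merely because carried values are constant. Conversely, a participant who leaves early with a score of 3 or more is fixed as a failure, although many such people would be expected to improve by Day 14 without treatment.

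Both errors enter the analysis on which the trial will be judged. They do not cancel unless dropout, its timing and the last scores are alike in the two arms. LOCF therefore cannot be defended here as conservative.

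**Working it through.** **Inputs from the protocol article, section 2.7.** Planning rates 88% (SFHS) and 48% (placebo); margin 10 points; two-sided alpha 0.05; power 90%; 2:1 allocation; 71 and 36 participants before dropout; 10% dropout; 80 and 40 enrolled.

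**The plan's own figure.** With unpooled variance, control n = [0.48×0.52 + (0.88×0.12)/2] × (1.960 + 1.282)² / (0.88 − 0.48 − 0.10)² = 35.3, rounded up to 36. Treatment n = 2 × 35.3 = 70.6, rounded up to 71. Dividing by 0.9 gives 79 and 40, which 80 and 40 cover. The sample size reproduces and is not at issue. The allowance of 10% of 120 is 12 people, used below as the amount of missing data.

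**Assumptions, not in the protocol.** Relief accrues linearly over 14 days without relapse; all dropouts in an arm leave at Day t; dropouts would have had the same Day 14 rate as completers. The split of dropout between arms is varied.

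**Formula.** For true rate p and dropout fraction d, the LOCF rate is (1 − d)·p + d·p·(t/14). With t = 4 this is p·(1 − d×10/14).

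| True rates | Dropout SFHS / placebo (people) | LOCF SFHS | LOCF placebo | LOCF difference | True difference |
|---|---|---|---|---|---|
| 60 / 60 | 5% / 20% (4 + 8 = 12) | 57.9% | 51.4% | +6.4 | 0 |
| 60 / 60 | 15% / 0% (12 + 0 = 12) | 53.6% | 60.0% | −6.4 | 0 |
| 60 / 60 | 10% / 10% (8 + 4 = 12) | 55.7% | 55.7% | 0.0 | 0 |
| 88 / 48 | 10% / 10% (8 + 4 = 12) | 81.7% | 44.6% | 37.1 | 40 |
| 88 / 48 | 15% / 0% (12 + 0 = 12) | 78.6% | 48.0% | 30.6 | 40 |

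First row in full: 0.95×0.60 + 0.05×0.60×4/14 = 0.579; 0.80×0.60 + 0.20×0.60×4/14 = 0.514; the unrounded difference is 0.064.

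**Range over timing.** When both true rates are 60%, the bias is 0.60 × (placebo dropout − SFHS dropout) × (1 − t/14). For 5% against 20% this is 0.09 × (1 − t/14): 9.0 points if the baseline score is carried (t = 0), 6.4 at Day 4, 4.5 at Day 7 and 2.6 at Day 10.

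**What this model leaves out.** It has no relapse, so every shift in the table comes from dropouts frozen as failures. None comes from false relief. A separate bound covers that. If a share s of dropouts in each arm carry a score of 2 or less, LOCF moves the difference by s × (SFHS dropout − placebo dropout), compared with counting dropouts as not relieved. With s from 50% to 100%, 15% against 0% moves it by +7.5 to +15.0 points, and 5% against 20% by −7.5 to −15.0. These are upper limits on the false-relief error, reached only if none of those people would have met the endpoint at Day 14. With equal dropout and the same s in both arms, the shift is zero.

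**The case against.** Several points can fairly be made for the plan.

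- Multiple imputation is already specified and will be reported beside LOCF, so the change is largely a re-ordering. That is true, but the primary result is still the LOCF result, and the one alternative rests on MAR.
- Early discontinuers, other than those lost to follow-up, "should complete subsequent visits according to the study schedule until the study endpoint" (section 2.8.2). This limits how many people LOCF touches. It stands as a mitigation; the 12-person figure assumes the whole planned allowance lacks Day 14 data.
- The article does not say whether the raw CSS or the derived relief status is carried. If status is carried, a one-day dip would not qualify. The 48-hour part of the point therefore holds only if the raw score is carried. The conflict over Day 14 status holds either way.
- The larger shifts need clearly unequal, early dropout. That is correct, and the equal-dropout rows show how small the effect is otherwise.

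A reader might also infer a stronger point: that people moved to other treatment are wrongly counted as relieved in the full analysis set. Section 2.8.1 says "Such participants will be withdrawn and provided with alternative treatments", visits continue, and only the per-protocol set removes users of medication affecting efficacy. The documents do not support calling this an error. Someone who scores 2 or less at Day 14, maintained for 48 hours, meets the endpoint as written. Analysing observed outcomes whatever else was taken is a recognised treatment-policy approach. Lack of efficacy is not among the listed (non-exhaustive) withdrawal reasons, and nothing says that the alternative treatments are antitussives or more frequent on placebo. The rule may also be in an analysis plan that is not shown. This is an estimand question for the sponsor to state.

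**Conclusion.** The point holds in a limited form. Within section 2.10, the rule that Day 14 status decides and the choice of LOCF as primary do not fit together, and LOCF suits a self-limiting condition poorly. LOCF can misclassify dropouts in both directions; it does not always do so, and it does not favour either arm by construction.

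Within the planned 10% dropout, the illustrated bias under the null is +6.4 or −6.4 points for strongly unequal Day 4 dropout and zero for equal dropout. At the planning rates, equal dropout costs 2.9 points (40 to 37.1). These sizes rest on linear accrual of relief, a common dropout day and assumed splits between arms, none of which the protocol gives. The conflict between the two rules rests on the text alone. It merits an amendment before unblinding but does not undermine the design.

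**What to change.** Amend section 2.10 as follows:

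- Make the planned multiple imputation the primary handling of missing data. Impute the daily CSS with the variables already listed, then derive the Day 14, 48-hour responder status in each imputed data set.
- Demote LOCF to a sensitivity analysis, and state whether it carries the score or the derived status.
- Add a delta-adjusted (tipping-point) sensitivity analysis, since the only planned alternative to LOCF assumes MAR.
- Separately, have the sponsor state how Day 14 scores recorded after alternative treatment are classed in the full analysis set. Either answer can be legitimate if it is stated in advance.

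The cost is a wording change, modest programming and slightly wider intervals than under LOCF. No new data are needed, because daily scores are already collected. One practical limit is that Table 1 has the diary card returned only at Visit 2. For people lost before then, the daily scores may be recoverable only in part, and the imputation can use only what is recovered. Recruitment is scheduled to November 2027, so there is time to make the change before unblinding.

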#### Secondary outcomes

2.6.2

(1) CSS: CSS will be recorded at baseline and daily. The differences in CSS between the two groups will be evaluated on day 7 and day 14.(2) CET: CET scores will be recorded at baseline, day 7, and day 14 to evaluate the inter-group differences in CET scores at these time points.

The Cough Evaluation Test (CET) is a concise, patient-reported questionnaire comprising 5 items that assess key dimensions of cough impact, including daytime cough frequency, sleep disturbance, cough intensity, interference with work and daily activities, and cough-related anxiety. Each item is rated on a 5-point Likert scale from 1 (never) to 5 (always/frequently). The total score ranges from 5 to 25, with higher scores indicating more severe cough-related impairment.

(3) TCM Syndrome Efficacy: TCM syndrome scores will be recorded at baseline, day 7, and day 14 to assess the inter-group differences in both the scores and the overall clinical efficacy of TCM syndromes.

The TCM syndrome score is an instrument used to assess the severity of symptoms associated with the Wind invasion-Dampness obstruction syndrome. It comprises three major symptoms—cough, throat discomfort, and symptom aggravation triggered by cold, heat, or irritant odors—and three minor symptoms, including oral stickiness, poor appetite, and abdominal distension. Major symptoms are graded on a 4-level scale (absent, mild, moderate, and severe), scored 0, 2, 4, or 6 points respectively; minor symptoms are scored 0, 1, 2, or 3 points. Tongue appearance and pulse condition are additionally recorded to confirm the syndrome diagnosis. The total score is the sum of all individual symptom scores, with higher scores indicating greater TCM syndrome severity.

(4) LCQ: LCQ scores will be recorded at baseline and on day 14 to evaluate the inter-group differences in the improvement of quality of life.

The LCQ is a health-related quality of life instrument specifically designed to assess the impact of cough across three domains: physical (8 items), psychological (7 items), and social (4 items). Each of the 19 items is rated on a 7-point Likert scale ranging from 1 to 7. Domain scores are calculated as the mean of the constituent items (range 1–7), and the total score is the sum of the three domain scores, ranging from 3 to 21, with higher scores indicating better cough-related quality of life.

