Secondary efficacy endpoint analysis: for quantitative variables, descriptive statistics will include number of cases (*n*), mean, standard deviation (SD), minimum, maximum, median, lower quartile (Q1), upper quartile (Q3), and 95% confidence interval (95%CI). Prior to analysis, normality tests will be performed for variable distributions: if the data conform to a normal distribution, inter-group comparisons will be conducted using the independent-samples *t* test, and within-group pre- and post-treatment comparisons will be conducted using the paired *t* test; if the data do not conform to a normal distribution, inter-group comparisons will be conducted using the Wilcoxon rank-sum test, and within-group pre- and post-treatment comparisons will be conducted using the Wilcoxon signed-rank test. For categorical variables, results will be described using frequencies and percentages. When considering the impact of center effects, binary and ordinal variables will be analyzed using the CMH χ^2^ test, and 95% confidence intervals for between-group risk differences will be provided for binary variables; when adjustment for baseline imbalance or other covariates is required, Logistic regression analysis will be used. For time-to-event variables, median time, lower and upper quartiles, and 95% confidence intervals will be described, Kaplan–Meier survival curves will be plotted, and inter-group comparisons will be performed using the log-rank test.

All statistical tests will be two-sided, and *p* < 0.05 will be considered statistically significant.

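### The quantitative secondary scores are compared by a t or Wilcoxon test picked by a normality pre-test, with no baseline-adjusted model named although every baseline score is collected

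*Protocol article*

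**What the plan says.** All four scores are measured before treatment. On two of them the protocol (Secondary outcomes, 2.6.2) states "CSS will be recorded at baseline and daily" and "CET scores will be recorded at baseline, day 7, and day 14". The same section and Table 1 put the TCM syndrome score at baseline, Day 7 and Day 14, and LCQ at baseline and Day 14.

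The Statistical analysis section (2.10) then fixes how quantitative secondary outcomes are compared:

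- Selector: "Prior to analysis, normality tests will be performed for variable distributions".
- Normal branch: "if the data conform to a normal distribution, inter-group comparisons will be conducted using the independent-samples" t test.
- Non-normal branch: "if the data do not conform to a normal distribution, inter-group comparisons will be conducted using the Wilcoxon rank-sum test".
- Before/after comparisons within each arm use the paired t test or, on the non-normal branch, "within-group pre- and post-treatment comparisons will be conducted using the Wilcoxon signed-rank test".

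Covariates appear once for secondary outcomes, in the sentence on binary and ordinal variables: "when adjustment for baseline imbalance or other covariates is required, Logistic regression analysis will be used". In that same sentence, centre enters only through the CMH test, and between-group confidence intervals are promised only for binary risk differences. No linear model, ANCOVA or mixed model is named anywhere in the article.

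The quantity compared is not defined. For CSS the text says "The differences in CSS between the two groups will be evaluated on day 7 and day 14", which suggests the scores at those days. For LCQ the aim is worded as improvement in quality of life, which suggests a change from baseline.

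**The concern.** The plan states a method here; it does not leave the method open. That method makes no stated use of the baseline score in the between-group comparison. For the primary endpoint, by contrast, the same section puts baseline CSS and centre into a supplementary logistic model and into the multiple imputation.

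Three things are at stake for the secondary scores:

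1. Precision, to the extent that baseline predicts outcome.
2. Protection against a chance baseline difference between 80 and 40 patients.
3. A stable, reported effect estimate. The pre-test lets the observed data decide which test is used. The Wilcoxon branch by itself gives a p value and no mean difference.

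The before/after tests within each arm add little evidence. The Interventions section calls the condition self-limiting, and the sample size assumes 48% relief on placebo, so both arms are expected to improve.

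**Working it through.** **The plan's own figure.** The only stated design figure is the sample size for the primary outcome (2.7). Inputs: rates 0.88 and 0.48, margin 0.10, two-sided 0.05, power 0.90, ratio 2:1.

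n(control) = (1.960 + 1.282)² × (0.48×0.52 + 0.88×0.12/2) / (0.88 − 0.48 − 0.10)² = 10.507 × 0.3024 / 0.09 = 35.3, giving 36 control and 71 treatment (2 × 35.3 = 70.6).

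107/0.9 gives 119, enrolled as 120. It reproduces, and nothing below touches it.

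**Inputs for this point.** Group sizes 80 and 40, and two-sided 0.05, are from the protocol. Three inputs are assumptions: the baseline-outcome correlation ρ, which the documents do not give; 80% power for the detectable difference; and a 0.5 SD effect for illustration. The change-score formula also assumes equal SDs at baseline and follow-up.

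**Formulas.**

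- Post-score comparison, 80% power: (1.960 + 0.842) × √(1/80 + 1/40) = 2.802 × 0.1936 = 0.543 SD.
- Change-score comparison: multiply by √(2(1−ρ)).
- ANCOVA: multiply the post-score figure by √(1−ρ²).
- Variance ratios: ANCOVA to post-score is 1−ρ². ANCOVA to change-score is (1−ρ²)/(2(1−ρ)) = (1+ρ)/2.

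| ρ (assumed) | ANCOVA / post variance | ANCOVA / change variance | Detectable: post | Detectable: change | Detectable: ANCOVA |
|---|---|---|---|---|---|
| 0.3 | 91% | 65% | 0.543 SD | 0.642 SD | 0.518 SD |
| 0.5 | 75% | 75% | 0.543 SD | 0.543 SD | 0.470 SD |
| 0.6 | 64% | 80% | 0.543 SD | 0.485 SD | 0.434 SD |

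For a true effect of 0.5 SD, power is 73.3% on post scores. On change scores it is 58.8% / 73.3% / 82.3%, and with ANCOVA 77.2% / 84.6% / 89.8%, at the same three values of ρ. With 72 and 36 patients after 10% dropout, the detectable difference is 0.572 SD on post scores against 0.546 / 0.495 / 0.457 SD with ANCOVA.

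**Chance imbalance.** The standard error of the baseline difference is 0.194 SD, so 95% of allocations fall within ±1.96 × 0.194 = ±0.38 SD. A baseline difference of δ shifts an unadjusted post-score difference by ρδ. At the 95% limit with ρ = 0.5, that is 0.5 × 0.38 = 0.19 SD. ANCOVA removes this shift.

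**Validity.** In a simulation with normal data, 80/40 patients, 2,000 runs and ρ from 0.3 to 0.7, type I error was 4.3% to 5.9% for the pre-tested choice on post scores, the same on change scores, and ANCOVA. At ρ = 0.5 and 0.5 SD, power was 71%, 73% and 84% respectively.

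**The selector applied to CSS.** CSS is an integer from 0 to 6 (Table 3). For rounded normal scores with an assumed SD of 1.3 and four pairs of arm means, a Shapiro-Wilk test (assumed, since the protocol names none) rejected normality in at least one arm in 100% of 2,000 runs. CSS would then go to Wilcoxon almost always.

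**The case against.** The strongest reply is that this is a matter of efficiency and not of error. That stands. Treatment is randomized, the outcomes are secondary, and the primary CMH analysis is already stratified by centre with a supplementary model that includes baseline CSS. A reader might infer bias or an inflated error rate from the two-stage testing. The simulation shows no noticeable inflation, and randomization protects the unadjusted comparison.

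A reader might also infer that the baseline scores are thrown away. The text does not support that. They enter the paired tests, and the LCQ wording may mean that a change score is compared. What is missing is a stated use of baseline in the between-group comparison.

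The size of the gain is also open. Saying that adjustment is worth one third more patients (1/0.75 = 1.33) holds only at ρ = 0.5, which the documents do not give. For CSS a lower ρ is plausible. Entry requires a score of at least 3, which narrows the baseline range. Relief means a score of 2 or less and is expected in 88% of the SFHS arm, which pushes Day 14 towards the floor. At ρ = 0.3 the detectable difference falls only from 0.543 to 0.518 SD. The figures also take the t test as comparator, which CSS would rarely receive.

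It is fair, too, that means, SDs and medians are reported whichever test is used, so a crude difference can be worked out. A formal difference with its interval is still not promised. If CSS were treated as ordinal, the CMH test would bring in centre but not baseline, and the article does not classify it so.

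Finally, a Gaussian repeated-measures model for a 0-6 score is debatable, and removing the within-group tests altogether is partly preference. The article never presents those tests as evidence of efficacy.

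**Conclusion.** The point holds as a worthwhile improvement to a stated method for secondary outcomes. The between-group tests for CSS, CET, TCM syndrome score and LCQ carry no baseline or centre term, are selected by a normality pre-test, and leave open whether post-treatment or change scores are compared.

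Under the usual large-sample linear-model assumptions, ANCOVA is at least as efficient as either reading. How much is gained depends on which reading is meant and on an unknown ρ. Across 0.3 to 0.6, the variance saving is 9% to 36% against post scores and 20% to 35% against change scores. Against post scores, the saving for CSS may sit at or below the low end. The benefits that depend least on ρ are a fixed estimand and a reported difference with its interval.

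**What to change.** In section 2.10:

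- Remove the normality test as the selector of method.
- For each score, prespecify ANCOVA with treatment, baseline score and centre. Where Day 7 and Day 14 both exist (CSS, CET, TCM syndrome score), a repeated-measures model with the same terms and treatment-by-visit is an alternative.
- Report the adjusted mean difference with its 95% CI at each planned visit. This also settles the post-versus-change question, because with baseline in the model both give the same treatment estimate.
- Keep a rank-based or ordinal analysis as sensitivity, especially for the 0-6 CSS.
- Label within-group before/after results as descriptive only.

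The change needs wording and standard SAS procedures, and no added data or patients. Recruitment is ongoing and blinded, so it can still be fixed before unblinding. If it is handled as a protocol amendment, section 2.1 requires ethics re-approval and a registry update.

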#### Inclusion criteria

2.3.1

Participants who meet all of the following criteria will be eligible for enrollment:

(1) Age: Aged 18–65 years (inclusive) at the time of informed consent.(2) Western Medicine Diagnosis: Meeting the diagnostic criteria for PIC.(3) TCM pattern identification: Wind invasion-Dampness obstruction syndrome.(4) Symptom Severity: CSS of ≥ 3.(5) Informed consent: Written informed consent was obtained.

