(5) Cough Cure and Relief Rates: Based on daily CSS records and predefined criteria, the inter-group differences in the cough cure rate (at day 7 and day 14) and the cough relief rate (at day 7) will be evaluated.(6) Time to Cough Cure and Relief: Based on daily CSS records, the inter-group differences in the median time to reach cough cure and relief within the 14-day period will be analyzed.(7) Cough Recurrence Rate: This is defined as the proportion of participants who achieved relief by the end of treatment but experienced a recurrence of cough during the 7-day post-treatment follow-up.

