### Sample size calculation

2.7

The sample size was estimated based on efficacy data from previous clinical trials. The cough relief rate for Suhuang Zhike Capsule was reported to be 87.75–93.33% (8, 14); thus, the expected relief rate for the Shufeng Huashi formula (π_T_) was estimated at 88%. The relief rate for the placebo, based on previous studies, ranged from 47.76–58.51% (15, 16); therefore, the expected relief rate for the placebo group (π_C_) was set at 48%. A 2:1 superiority design was employed, with a two-sided significance level of *α* = 0.05 and a power of 0.9 (1 − *β* = 0.9). A clinical superiority margin of 10% was considered. Using PASS 21 software for sample size estimation, the calculated requirement was 71 participants for the treatment group and 36 for the control group. Accounting for a 10% dropout rate and potential unforeseen data loss during trial execution, a total of 120 participants will be enrolled, with 80 in the treatment group and 40 in the control group. Participants will be recruited through outpatient clinics and advertisements.

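### For Day 7 relief and Day 7 and Day 14 cure, covariate adjustment depends on a need judged after baseline data are seen; one fixed analysis adjusting for centre and baseline CSS would be better

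*Protocol article*

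**What the plan says.** Section 2.6.2, item (5), names the outcomes concerned: "the inter-group differences in the cough cure rate (at day 7 and day 14) and the cough relief rate (at day 7) will be evaluated".

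Section 2.10 gives binary secondary outcomes two routes, each introduced by a condition:

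- CMH: "When considering the impact of center effects, binary and ordinal variables will be analyzed using the CMH χ^2^ test", with the addition that "95% confidence intervals for between-group risk differences will be provided for binary variables".
- Logistic regression: "when adjustment for baseline imbalance or other covariates is required, Logistic regression analysis will be used".

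The sentence sets no criterion for when adjustment is needed and does not say which result leads. It plans no risk difference from the logistic model.

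For the primary endpoint, the same section fixes a centre-stratified CMH test with a risk difference and adds that "supplementary Logistic regression analyses will be performed with treatment group, center, and baseline CSS score as covariates". That model does not depend on any observed imbalance.

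**The concern.** In a randomised trial a baseline difference between arms is due to chance. The reason to adjust is that a covariate predicts the outcome, and that can be judged before any data exist. A rule that waits for imbalance uses the wrong criterion and leaves the choice of analysis open until baseline data are seen.

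Baseline CSS is a clear candidate. Entry requires "Symptom Severity: CSS of ≥ 3", and Table 3 caps the total at 3 + 3 = 6. Relief means a total of 2 or less and cure 1 or less. A participant entering at 3 must drop 1 point for relief and 2 for cure; one entering at 6 must drop 4 and 5. The plan already uses baseline CSS as a covariate and as an imputation variable for the primary endpoint.

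Two things are at stake. Two analysts following the text could present different lead results for one endpoint, perhaps on different scales. Some precision on the secondary comparisons would also be given up.

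**Working it through.** **1. The plan's own figure.** Section 2.7 sizes the trial for the primary endpoint only: "A 2:1 superiority design was employed, with a two-sided significance level of *α* = 0.05 and a power of 0.9", with 88% vs 48% and a margin of 10 points. The unpooled formula gives n(control) = (1.960 + 1.282)² × (0.88 × 0.12 / 2 + 0.48 × 0.52) / (0.40 − 0.10)² = 10.507 × 0.3024 / 0.09 = 35.3, so 36. Treatment is 2 × 35.3 = 70.6, so 71. The stated 71 and 36 are reproduced and this point does not touch them. The article gives no rates or power for the secondary outcomes.

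**2. The two scales differ.** At the planning rates the risk difference is 0.88 − 0.48 = 0.40. The odds ratio is (0.88/0.12) / (0.48/0.52) = 7.333 / 0.923 = 7.9. If the adjusted model became the reported result in its usual form, the effect would be on another scale.

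**3. What always adjusting gains.** Day 7 rates, cure rates and the CSS–outcome association are not in the article, so everything here is assumed. Both simulations use 80 vs 40 and a two-sided 5% level, and neither includes centre.

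*Simulation A* (2,000 trials per setting): baseline CSS 3/4/5/6 in 30/35/20/15%; log-odds of response falling by 0.5, 0.8 or 1.1 per CSS point. It compares a two-sample proportion test, a Mantel-Haenszel test stratified by baseline CSS, and the stratified test used only when baseline CSS differs between arms at p < 0.05.

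| Assumed rates | Unadjusted power | Triggered at p < 0.05 | Always adjusted | Gain (points) |
|---|---|---|---|---|
| 60% vs 35% | 73 / 71 / 72% | 73 / 71 / 72% | 75 / 77 / 82% | 2 / 6 / 10 |
| 70% vs 48% | 66 / 64 / 67% | 66 / 65 / 68% | 67 / 69 / 76% | 1 / 5 / 9 |

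At 88% vs 48% power already exceeds 99%, so nothing is gained where the true difference is that large.

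*Simulation B* (6,000 trials per setting): baseline CSS effect of 0.5, 0.8 or 1.2 log-odds per SD; treatment log-odds ratio 1.2; resulting rates about 41–44% vs 66–68%.

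| CSS effect per SD | Unadjusted power | Trigger p < 0.05 | Trigger p < 0.10 | Trigger p < 0.20 | Always adjusted | Gain (points) |
|---|---|---|---|---|---|---|
| 0.5 | 0.822 | 0.823 | 0.824 | 0.827 | 0.840 | 1.8 |
| 0.8 | 0.759 | 0.765 | 0.768 | 0.777 | 0.811 | 5.2 |
| 1.2 | 0.635 | 0.645 | 0.656 | 0.670 | 0.758 | 12.3 |

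The variance of the risk difference falls by 1 − 0.946 = 5%, 1 − 0.878 = 12% and 1 − 0.773 = 23%.

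**4. How much a trigger keeps.** Let Z be the standardised baseline difference and c the two-sided critical value at trigger level a. The share of the variance gain kept is E[Z²; |Z| > c] = a + 2cφ(c), where φ is the standard normal density.

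- a = 0.05: 0.05 + 2 × 1.960 × 0.0584 = 0.28
- a = 0.10: 0.10 + 2 × 1.645 × 0.1031 = 0.44
- a = 0.20: 0.20 + 2 × 1.282 × 0.1755 = 0.65

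Simulation B gives 0.28–0.30, 0.43–0.47 and 0.63–0.67. In power terms less is kept. At the middle setting a p < 0.05 trigger recovers (0.765 − 0.759) / (0.811 − 0.759) = 0.006 / 0.052, about 12% of the gain; a p < 0.20 trigger recovers 0.018 / 0.052, about 35%.

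**5. Agreement and error rate.** The adjusted and unadjusted analyses disagree on significance in about 5%, 10% and 18% of Simulation B trials. With no treatment effect and a prognostic baseline CSS (4,000 trials per setting), a p < 0.05 trigger applied mechanically rejects in 0.043–0.050. Counting a rejection whenever either analysis is significant gives 0.058–0.071. The Monte Carlo standard error is √(0.05 × 0.95 / 4000) = 0.003.

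**The case against.** The strongest reply is that the sentence is looser than an imbalance-only rule. It also allows adjustment for other covariates, so baseline CSS could be included without any observed imbalance. Nor does it say that logistic regression replaces CMH. Risk-difference intervals are promised for binary variables in general, and the primary endpoint uses CMH with a supplementary logistic model alongside. Both observations are right. A reader might infer that adjustment happens only on imbalance, or that the risk difference is certain to be dropped; the text supports neither. What remains is that the broader wording is just as undefined about when adjustment is needed, and that no lead result is named.

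A second reply is that covariate lists and operating criteria belong in an SAP, which is not shown. That holds for the list and the threshold. It does not cover the condition itself, which the article states and which a faithful SAP would carry forward.

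A third reply concerns the numbers. Rates and slopes are assumed and centre is left out. Simulation A tests a CSS-stratified method and not the model recommended here. Its Monte Carlo error is about √(0.7 × 0.3 / 2000) = 1 point, as large as its smallest gain. All of this stands, so the power figures are illustrative only.

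A reader might also infer that the plan obtains almost none of the available precision. That rests on a p < 0.05 trigger the plan does not state, and even there about 28% of the variance gain is kept.

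**Conclusion.** The point holds as a modest matter of pre-specification and efficiency on secondary outcomes. The article makes adjustment of Day 7 relief and Day 7 and Day 14 cure depend on a need judged after baseline data are seen, although a fixed covariate set is named for the primary endpoint. The conditional wording is a defect without any simulation.

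The size of the loss is uncertain. Under the assumed rates and CSS effects, always adjusting adds roughly 1 to 12 power points, about 5 to 6 at the middle assumptions, and nothing useful if the true difference is near 40 points. An imbalance trigger keeps part of this, about 28% to 65% of the variance gain for triggers between p < 0.05 and p < 0.20.

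A reader might infer an inflated false-positive rate. The documents do not support that: the trigger refers to baseline data, a mechanical rule holds the level, and inflation appears only if outcome results steer the choice, which nothing in the text licenses. The primary analysis and the sample size are unaffected.

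**What to change.** In section 2.10, delete the condition on baseline imbalance or other covariates for these three endpoints. State one analysis that is always used: for example, a logistic model with treatment, centre and baseline CSS, reported as a standardised risk difference with 95% CI. Name it as the lead result and report the centre-stratified CMH result as supportive. The covariates are those already named for the primary endpoint's supplementary model.

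The cost is wording and a little SAS code; baseline CSS is already collected. Recruitment is planned to 30 November 2027, so the change can be settled before unblinding. If it is made as a protocol amendment, section 2.1 requires ethics re-approval and a registry update.

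There are two drawbacks. The variance becomes model-based, and small centres may need pooling. With six hospitals the average is 120 / 6 = 20 participants per centre, of whom 40 / 6, about 7, are on placebo, and competitive enrolment may leave some centres well below that. A pooling rule should be fixed in advance, without reference to outcomes.
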